### Design

2.1

To evaluate the change of myocardial viability in single CTO patients with successful PCI or with only OMT, we propose to conduct a prospective, nonrandomized multicenter trial using with a DA. The Ethics Committee in The First Affiliated Hospital of Dalian Medical University approved all study procedures. Patients and interventional cardiologists for this trial are to be recruited at 4 hospitals. All cardiologists have more than 10 years of PCI experience and perform CTO cases at least 50 cases each year.

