### Treatment details

4.2

At baseline, 3 months, 6 months, and 12 months recommendations for therapy are made to the physicians in line with guideline.^[18]^ The goal of antihypertensive therapy is to achieve a blood pressure of less than 140/80 mm Hg. The aim of antilipid therapy is to achieve levels of low-density lipoprotein (LDL) < 1.8 mmol/L. In the first instance, statin therapy will be initiated and then increased with the addition of a second agent if necessary. For patients with a BMI of > 25 kg/m^2^, the physicians are asked to refer the patient for dietary advice. Similarly, smokers are referred to the smoking cessation clinic. In the case of diabetics with raised blood sugar, the physicians are asked to measure HbA1c and to ensure that the patients’ subsequent therapy is tailored to achieve an HbA1c of less than 6.5 mg/dL. OMT included antiplatelet medication, β-blockers, rennin angiotensin system blockers, nitrates, calcium channel blockers, and aggressive lipid lowering therapy. The decision to pursue invasive treatment as well as site of access, type of stents, use of intravascular ultrasound, and use of glycoprotein IIb/IIIa receptor inhibitors was left to the discretion of the physician. Prior to PCI, all patients were pretreated with loading doses of aspirin (300 mg) and clopidogrel (300–600 mg) unless they were previously medicated with these antiplatelet agents. PCI was performed using contemporary techniques such as bilateral injections, specialized stiff hydrophilic wire with a tapered tip, and microcatheters in a retrograde approach, when available. All interventions and procedural anticoagulations were performed in accordance with current standard guidelines.^[19]^

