## Sample size calculation

7

The main goal of this study is to estimate the improvement of myocardial viability associated with different treatment strategies evaluated by PET/CT. Thank you for your kind comments. We set the sample size by 2 means. First, at the time of study design and commencement, no studies examined the effect of PCI and/or OMT on myocardial viability in single-vessel CTO. Therefore, it is difficult to calculate a target number of patients that should achieve the primary endpoint. For this reason, we consulted with statisticians and set sample size to 200 patients according to previous studies on CTO, which is more than previous studies and feasible to realize. Second, retrospective data indicates that about 80% patients could reach the improvement rate of 5% by PCI, which indicates significant. Approximately 20% patients treated with OMT only can be improved more than 0.5%. We hypothesize that 40% patients’ myocardial viability of both groups could be improved significantly. A total of 131 patients is needed to reject the null hypothesis of no difference between groups (2-sided test *χ*^2^ test, power 90%, α=0.05). Allowing for a 15% drop-out rate, 151 patients will be recruited. Since this is a multicenter study, the sample size was enlarged to 200 patients.

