## Statistical analysis

8

Normally distributed continuous variables were presented as the mean ± SD, variables with a skewed distribution as the median together with interquartile range (IQR). Categorical variables are expressed as percentages. Changes in data measured by PET/CT, CMR, and TTE will be summarized by mean, standard deviation, minimum, median, and maximum. Differences between groups, including baseline characteristics, will be compared using a *t* test, Wilcoxon rank-sum test, or *χ*^2^ test. The correlation between treatment strategies and viable myocardium will be analyzed by liner regression analysis.

For the safety evaluation, the number and prevalence of MACEs will be calculated. The Kaplan–Meier method was used to illustrate the timing of events during follow-up in relation to treatment strategies and statistical assessment was performed with the log-rank test. The prognostic value of treatment strategies was assessed by investigating its relation with the composite outcome in Cox proportional-hazards analyses.

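### The sample is enlarged to 200 because the study is multicentre, but no basis is given and no named analysis mentions centre, so the unadjusted comparisons stay open to confounding by hospital

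*Protocol article*

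**What the plan says.** All references are to the protocol article.

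- **Section 7 (Sample size calculation)** arrives at 131 patients for a two-sided chi-square test ("power 90%, α=0.05"), raises this to 151 for 15% dropout, and then states: "Since this is a multicenter study, the sample size was enlarged to 200 patients". The same section also supports 200 by reference to earlier CTO studies and feasibility.
- **Section 2.1 (Design)** describes a non-randomised trial: "Patients and interventional cardiologists for this trial are to be recruited at 4 hospitals". By the Abstract, groups follow the patient's choice after use of a decision aid.
- **Section 4.2 (Treatment details)** leaves several matters to the physician's discretion, among them "The decision to pursue invasive treatment as well as site of access, type of stents, use of intravascular ultrasound".
- **Section 8 (Statistical analysis)**: "Differences between groups, including baseline characteristics, will be compared using a" t test, a Wilcoxon rank-sum test or a chi-square test. It continues: "The correlation between treatment strategies and viable myocardium will be analyzed by liner regression analysis". Events are compared by Kaplan-Meier curves, a log-rank test and Cox models. Centre appears nowhere in the section as a factor, stratum or covariate, and no covariates are listed for either model.

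**The concern.** In the calculated route to 200, the multicentre structure is the only reason for the last 49 patients, so the plan regards that structure as important. Its only visible response is a larger N. That does not address the problem several hospitals create in this design.

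Nothing balances treatment within hospital. If hospitals differ in how many patients have PCI and also in average change in viability, part of the difference between hospitals enters the PCI-versus-OMT difference. With four hospitals, that part does not shrink as patients are added, whereas the standard error of an unadjusted test does. At stake is whether the primary comparison keeps its stated 5% error rate, and whether a difference between hospitals could be reported as a treatment effect.

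**Working it through.** **1. The plan's own figures.** 131 × 1.15 = 150.65, so 151 is reproduced as a simple 15% uplift (131/0.85 would give 155). The step to 200 is a factor of 200/151 = 1.325 with no formula behind it. Read as a cluster design effect with 50 patients per hospital, it would imply an ICC of (1.325 − 1)/49 = 0.0066. The article does not state this value, and that formula suits whole hospitals on one treatment, which is not the case here.

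Separately, 131 does not follow from the stated rates ("about 80% patients could reach the improvement rate of 5% by PCI"; "Approximately 20% patients treated with OMT only can be improved more than 0.5"% under OMT). For 80% against 20%, n per arm = [1.96√(2 × 0.5 × 0.5) + 1.2816√(0.16 + 0.16)]² / 0.6² = 2.111²/0.36 = 12.4, so 13 per arm and 26 in total. That is a different matter and is not pursued here.

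**2. Inputs to the check.** From the article: 4 hospitals, two-sided alpha 0.05, N = 131, 151 and 200, 15% dropout, and 240 enrolled by November 2017 (section 3). Assumed, because the article gives no values: hospitals of equal size, half of all patients on PCI, ICC between 0.01 and 0.10, four patterns of PCI share by hospital, and no true treatment effect.

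**3. Formula.** Let a and b be a hospital's share of the PCI arm and of the OMT arm, and let D be the sum over hospitals of (a − b)². With total variance 1, the unadjusted mean difference has true variance (1 − ICC) × 4/N + ICC × D, while the unadjusted test uses about 4/N. The ratio is

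R = (1 − ICC) + ICC × D × N/4,

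and the false-positive rate is 2[1 − Φ(1.96/√R)].

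**4. Worked case: shares 20/40/60/80%, ICC 0.05, N=200.** PCI counts are 10, 20, 30 and 40 out of 100, so a − b is −0.3, −0.1, 0.1 and 0.3, and D = 0.09 + 0.01 + 0.01 + 0.09 = 0.20. True variance is 0.95 × 0.02 + 0.05 × 0.20 = 0.019 + 0.010 = 0.029, against 0.020. R = 1.45, 1.96/√1.45 = 1.63, and the rate is 10.4%.

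**5. Range at N=200 (formula).**

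| PCI shares (%) | D | ICC 0.01 | ICC 0.02 | ICC 0.05 | ICC 0.10 |
|---|---|---|---|---|---|
| 50 in all | 0 | 4.9% | 4.8% | 4.4% | 3.9% |
| 40/47/53/60 | 0.0218 | 5.0% | 5.0% | 5.1% | 5.1% |
| 30/43/57/70 | 0.0898 | 5.4% | 5.8% | 7.1% | 9.2% |
| 20/40/60/80 | 0.20 | 6.0% | 7.1% | 10.4% | 15.5% |

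A simulation with 4,000 runs per setting, which adds chance variation in the shares, gave at ICC 0.05 and 0.10 respectively: 6.0% and 6.1% (40-60%), 7.1% and 10.9% (30-70%), 10.8% and 16.8% (20-80%).

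**6. Does a larger N help?** R contains ICC × D × N/4, so for any D above zero it rises with N. For shares of 20-80% and ICC 0.05:

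- N=131: R = 0.95 + 0.01 × 131/4 = 1.278, rate 8.3%
- N=151: R = 1.328, rate 8.9%
- N=170 (200 less 15% dropout): R = 1.375, rate 9.5%
- N=200: R = 1.45, rate 10.4%
- N=240: R = 1.55, rate 11.5%

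The test exceeds 5% only when D > 4/N, which is 0.02 at N=200. Shares of 40-60% are almost exactly at that point.

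**7. With centre in the model.** In simulation, regression with centre as a fixed effect gave 4.2-6.0% in every setting (Monte Carlo error about 0.35 points). The simulation makes treatment unrelated to prognosis within hospital.

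These figures concern the difference in means. The chi-square and log-rank tests were not quantified separately, but the mechanism is the same.

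**The case against.** **Centre may be in an analysis plan that is not shown.** Linear regression and Cox models can carry centre, and a condensed article need not list covariates. This stands for those two methods: a reader might infer that every named analysis ignores centre, and the article does not establish that. It does not cover the t test, Wilcoxon, chi-square and plain log-rank, which as named have no place for centre. Nor would a later plan supply the missing reason for 200.

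**The multicentre sentence is not a claim about clustering.** True. Section 7 mentions neither correlation nor a design effect, and it supports 200 on other grounds as well. The point is therefore that the stated reason has no basis, not that a clustering calculation is wrong.

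**The error rate need not rise.** A reader might infer that the false-positive rate roughly doubles. The article does not support that as a general statement. A rate of 10% needs R of about 1.42. At N=200 that means shares of 20-80% with ICC near 0.05 (0.42/9 = 0.047), or 30-70% with ICC somewhat above 0.10 by the formula (0.42/3.49 = 0.12). Shares of 40-60% cannot reach it. At the ICC of about 0.007 implied by 200/151, even shares of 20-80% give only about 6%.

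**The design limits differences between hospitals.** Central blinded image reading, experience requirements for operators, common treatment targets, one decision aid and an endpoint measured as change from baseline may all lower the ICC. This is fair, and it favours the lower part of the range. None of them equalises PCI shares.

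**This is confounding, and centre adjustment does not cure it all.** Correct. With equal shares, ignoring centre is slightly conservative, so the inflation comes wholly from confounding by centre. Patient-level confounding within hospitals is untouched.

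**Conclusion.** The point holds in a limited form. Section 7 gives multicentre status as the reason for 49 further patients without a basis, section 8 names no analysis that uses centre, and its group comparisons are unadjusted in a trial where treatment is chosen. Adding patients does not remove confounding by hospital and, where shares differ, makes the unadjusted test somewhat worse.

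The size cannot be fixed from the article. At N=200 it runs from about 4% (equal shares), through 5-6% (40-60%) and 7% (30-70%, ICC 0.05), to about 10% (20-80%, ICC 0.05; 9.5% at 170 evaluable) and about 16% (20-80%, ICC 0.10). Every figure rests on an assumed ICC, assumed PCI shares and hospitals of equal size. The change is worth making because it is cheap, not because a large error has been shown.

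**What to change.** **Section 8.** Take the primary between-group estimate from the linear regression of the 12-month change in viability on treatment group, with centre (4 hospitals) as a fixed effect. Stratify the log-rank test and the Cox model by centre. For binary endpoints, use a centre-stratified test such as Cochran-Mantel-Haenszel where event counts allow.

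**Section 7.** Drop the multicentre reason for 200, or state the ICC or design effect behind it. Feasibility is already given there and can stand as the reason.

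**Cost.** Only wording changes; each patient's hospital should already be on record. The analysis gives up 3 degrees of freedom, and some precision if PCI shares differ strongly between hospitals. The text should say that this handles differences between hospitals only and leaves patient-level confounding within them.

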## Statistical analysis

8

Normally distributed continuous variables were presented as the mean ± SD, variables with a skewed distribution as the median together with interquartile range (IQR). Categorical variables are expressed as percentages. Changes in data measured by PET/CT, CMR, and TTE will be summarized by mean, standard deviation, minimum, median, and maximum. Differences between groups, including baseline characteristics, will be compared using a *t* test, Wilcoxon rank-sum test, or *χ*^2^ test. The correlation between treatment strategies and viable myocardium will be analyzed by liner regression analysis.

For the safety evaluation, the number and prevalence of MACEs will be calculated. The Kaplan–Meier method was used to illustrate the timing of events during follow-up in relation to treatment strategies and statistical assessment was performed with the log-rank test. The prognostic value of treatment strategies was assessed by investigating its relation with the composite outcome in Cox proportional-hazards analyses.

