**Methods and results::**

The risks and the benefits of both options (PCI and OMT) were listed in a CTO decision aid (DA). Eligible participants detected by invasive coronary angiography (ICA) or coronary computed tomography angiography (CCTA) were divided into PCI or OMT groups according to patients’ choice after shared-decision making process with DA. Participants will undergo positron emission tomography/computed tomography (PET/CT), cardiac magnetic resonance (CMR) and transthoracic echocardiography (TTE), and proceed to ICA and revascularization if possible. Blinded core laboratory interpretation will be performed for ICA, CCTA, PET/CT, CMR, and TTE. All participants will be followed up for 12 months. The primary endpoint is the improvement to the decrease of myocardial viability from baseline assessed with the use of PET/CT after 12-month follow-up.

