## Introduction

1

A chronic total occlusion (CTO) is defined as a complete coronary arterial obstruction with Thrombolysis In Myocardial Infarction (TIMI) flow grade of 0 for longer than 3 months.^[1]^ CTOs have been identified in up to 20% of all patients referred for diagnostic angiography.^[2]^ However, the CTO procedural success rate is 60% to 70%, much lower compared with non-CTO percutaneous coronary intervention (PCI) success rate of 98%.^[2,3]^ In the past, patients with a CTO were often managed conservatively or surgically rather than with PCI.^[4]^ The barriers that only 8% to 15% of patients with CTO face during PCI-based revascularization are numerous^[5–7]^: lower expectation of procedural success; higher perceived risk of complications; increased technical complexity; motivation; and training or catheter lab resources.^[8]^ Due to improvements in technique and observational evidence that successful CTO intervention is associated with symptomatic relief of angina, lower rates of subsequent myocardial infarction (MI) and coronary artery bypass graft (CABG), and survival improvement,^[9–16]^ there is growing interest in percutaneous treatment of CTO. Not only European but also American guidelines have assigned a class IIa (level of evidence B) recommendation for CTO PCI. However, there is currently no consensus on which strategy is much better. As a result, we divided patients into different groups using decision aid (DA) instead of randomization to protect the interests of patients as well as to increase compliance.

It is well known that the amount of viable myocardium is the best indicator of long-term cardiac event-free survival after cardiac intervention.^[17]^ Most CTO registries do not report preprocedural ischemic burden or myocardial viability. As such, the benefits of successful CTO PCI may be underestimated by the inclusion of patients with no viability or little ischemia that could not be expected to benefit from a successful procedure.

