Several studies have shown that CTO-PCI is associated with clinical improvement.^[20]^ Cardona et al^[21]^ studied 29 patients with heart failure with reduced ejection fraction (HFrEF) and evidence of viability and/or ischemia within the territory supplied by the CTO, and improvement in ejection fraction, left ventricular end-systolic volume and ischemia burden was observed after CTO-PCI. Hwang et al^[22]^ compared clinical outcomes of PCI with those of OMT alone in patients with CTO of a single coronary artery. Four hundred thirty-five patients with CTO of a single coronary artery were analyzed. After a median follow-up duration of 47.6 months, MACEs were noted for 16 patients in the OMT group compared with 41 patients in the PCI group. After propensity-score matching, there were no significant differences between the OMT group and PCI group with respect to MACE frequency or cardiac death. However, the study did not routinely evaluate the amount of viable myocardium or ischemia of study patients using functional ischemia testing. One of the most critical steps in the management of the patients with obstructive coronary heart disease is to determine ischemic burden whether or not the patient is symptomatic. It is well known that stress radionuclide myocardial perfusion imaging (rMPI) may distinguish patients at high risk (more than 5% annual mortality rate) from those at intermediate risk (1% to 5% annual mortality rate) or low risk (<1% annual mortality rate).^[22]^ It was reported that the presence of extensive ischemia (extent of ischemia >10%), ischemia in multiple segments, ischemia in more than 1 coronary artery territory, LVEF < 45%, large fixed defects, transient or persistent left ventricular cavity dilatation and increased lung uptake of thallium on rMPI denotes high risk for increased risk of cardiac events.^[23–25]^ Safley et al^[26]^ showed that PCI in patients with CTOs significantly decreased the ischemic burden from 13.1% to 6.9%. In that clinical study most of the patients had moderate to severe ischemic burden before treatment. On the other hand, it was shown that there was improved survival following revascularization (PCI or CABG) only in the presence of moderate to severe baseline ischemic burden used by rMPI in coronary artery patients. The appropriate use criteria heavily emphasize ischemic burden and suggest that revascularization is appropriate in cases with large territories of ischemia, even without symptoms.^[27,28]^ Stuijfzand et al^[29]^ demonstrated that CTO patients with documented ischemia and viability showed significant improvement in stress MBF and a reduction of ischemic burden after successful percutaneous revascularization. However, the duration from PCI to follow-up imaging was 99 days, which may underestimate the effect of procedures. Second, the patients’ symptoms or quality of life before and after treatment were not sufficiently documented. Last, although the anatomical SYNTAX score is an important tool to establish the optimum revascularization approach in patients with complex coronary heart diseases including CTO, SYNTAX score II can better score than anatomical SYNTAX to reach the best treatment alternative. A combination of anatomical SYNTAX score with 3 simple clinical variables (age, creatinine, or creatinine clearance, LVEF) has been shown to contain most of the prognostic information in predicting mortality after PCI.^[30,31]^ From that point of view it should be better to use SYNTAX score II.

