
## Conclusions

10

This study will be the first multicenter study to evaluate the effect of PCI and/or OMT on myocardial viability in patients with single-vessel CTO using combined PET/CT during long-term follow-up. The patients were divided after shared decision making process, which can protect the interests of patients as well as increase compliance. Furthermore, the study will show the effects of PCI and/or OMT strategies on the clinical outcomes in patients with CTO of a single coronary artery. Thus, SOS comedy will indicate the optimal treatment modality for single lesions resulting in CTO.

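### Patients choose their treatment, but the tests fixed for viability and MACE do not adjust for confounding, and no other control for it is mentioned

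*Protocol article*

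**What the plan says.** **How groups form.** The Abstract says eligible participants "were divided into PCI or OMT groups according to patients’ choice after shared-decision making process with DA". The Introduction gives the intent: "we divided patients into different groups using decision aid (DA) instead of randomization". Section 2.1 (Design) calls the trial nonrandomized and multicenter. Section 4.2 (Treatment details) also leaves the decision for invasive treatment to the physician.

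**How groups are compared.** Section 8 states: "Differences between groups, including baseline characteristics, will be compared using a" t test, Wilcoxon rank-sum test or chi-square test. For viability it adds: "The correlation between treatment strategies and viable myocardium will be analyzed by liner regression analysis". For MACE it uses Kaplan–Meier curves with a log-rank test, and then: "The prognostic value of treatment strategies was assessed by investigating its relation with the composite outcome in Cox proportional-hazards analyses".

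**What is not mentioned.** No covariate, stratification, matching, weighting or propensity score is named for this study. Section 9 (Discussion and limitations) does report an earlier PCI versus OMT comparison in single-artery CTO that used one: "After propensity-score matching, there were no significant differences between the OMT group and PCI group with respect to MACE frequency or cardiac death".

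**What will be claimed.** Section 10 (Conclusions) ends: "Thus, SOS comedy will indicate the optimal treatment modality for single lesions resulting in CTO".

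**The concern.** When patients choose, the arms can differ at baseline in ways that also affect outcome. The document itself points to such factors. The Introduction says patients without viability or with little ischemia could not be expected to benefit. Section 9 names age, creatinine and LVEF as carrying much of the prognostic information after PCI. The decision aid (section 4.1) covers complications, costs, contrast nephropathy and radiation, so choice may well follow a patient's risk and means.

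A test that treats the arms as exchangeable then estimates the treatment effect plus whatever difference goes with choosing PCI. Comparing baseline characteristics between groups may reveal some imbalance, but it corrects none. At stake are the primary comparison, the MACE comparison and the statement about the best treatment that the study means to draw from them.

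**Working it through.** **Step 1: what each stated method can do.** The plan gives no figure for imbalance or bias, so there is none to reproduce. The methods in section 8 are:

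| Method | Can it adjust? | What section 8 states |
|---|---|---|
| t, Wilcoxon, chi-square | No | Group comparison only |
| Log-rank | Only by strata | No strata named |
| Linear regression | Yes | Treatment strategy the only term named |
| Cox model | Yes | Treatment strategy the only term named |

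The chi-square calculation in section 7 is likewise an unadjusted two-group comparison.

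**Step 2: illustration of what is at risk.**

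Inputs from the document: planned size 200, drop-out 15%, two-sided α = 0.05, and an overall response of 40% (section 7).

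Assumptions, not in the document: a 1:1 split, no true treatment effect, and one binary baseline factor with the prevalences and response rates shown below.

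- Patients per arm: 200 × 0.85 / 2 = 85.
- Response in an arm = prevalence × response with the factor + (1 − prevalence) × response without it.
- PCI: 0.60 × 0.60 + 0.40 × 0.20 = 0.44. OMT: 0.40 × 0.60 + 0.60 × 0.20 = 0.36. Spurious difference d = 0.08; pooled rate 0.40.
- SE under the null = √(0.40 × 0.60 × 2/85) = 0.0751.
- Actual SE = √((0.44 × 0.56 + 0.36 × 0.64)/85) = 0.0749.
- Rejection rate = Φ((d − 1.96 × SE null)/SE actual) + Φ((−d − 1.96 × SE null)/SE actual) = Φ(−0.898) + Φ(−3.035) = 0.186.

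The same formula over a range of assumptions, at 85 per arm:

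| Factor prevalence, PCI v OMT | Response without → with factor | Spurious difference | Rejection rate |
|---|---|---|---|
| 55% v 45% | 30% → 50% | 2 points | 5.8% |
| 60% v 40% | 30% → 50% | 4 points | 8.3% |
| 60% v 40% | 20% → 60% | 8 points | 18.6% |
| 70% v 30% | 20% → 60% | 16 points | 56.8% |

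**Step 3: sensitivity to size and split.** Section 3 reports 240 enrolled. With 240 × 0.85 / 2 = 102 per arm, the third row becomes 21%. Splitting the 170 evaluable patients 2:1 (113 and 57) gives about 17% whichever arm is larger. The result depends mainly on the assumed imbalance and on the strength of the factor.

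**The case against.** **The models may be multivariable.** Section 8 does not say that the linear or Cox model is univariable. A linear regression on a two-level strategy alone would repeat the equal-variance t test, so listing it separately could mean that covariates are intended. A journal article may leave a covariate list and a centre term to the full protocol or analysis plan, which is not shown. This stands: a reader might infer that every planned analysis is unadjusted, or that centre is ignored, and the document does not establish either. It does not rescue the tests that section 8 fixes, or the absence of any stated intention to control confounding in a design that forgoes randomization.

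**Baseline is already used.** The primary endpoint is change from baseline, so baseline viability is subtracted. That is true. A reader might go further and infer a calculable bias from regression to the mean. That requires both self-selected groups to regress to a common mean, which the document cannot show. If the groups differ stably and would otherwise follow parallel trends, the change score is unbiased and baseline adjustment introduces the bias. No figure is given here for that reason.

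**The illustration rests on assumptions.** It does. It also takes a true null, whereas section 7 expects response of about 80% with PCI and 20% with OMT, although at different thresholds. A spurious 8 to 16 points would not explain a gap of 60.

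**The wording is often associational.** Section 8 speaks of correlation and prognostic value, and the design is openly described as nonrandomized. Unadjusted p-values remain valid for the unadjusted association. What fails is the treatment recommendation in section 10.

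**Conclusion.** The point holds. Treatment is chosen by the patient, the simple tests fixed in section 8 are unadjusted, the two regression models name treatment strategy as their only term, and no control for confounding is mentioned. Followed as written, the viability and MACE comparisons are not protected against confounding by choice and cannot show which modality is optimal.

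This is not proof that the results will be biased. Neither the size nor the direction of bias can be derived from the document. The rejection rates, about 19% in the worked case and about 6% to 57% over the range shown, rest wholly on assumed imbalances and response rates, a 1:1 split and no true effect. They show that the risk can matter, not how large it is here.

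**What to change.** - **Primary analysis.** Name one model for 12-month viable myocardium (% LV), either covariate-adjusted or propensity-score weighted. Include baseline viability, LVEF, age and centre, plus other prespecified confounders where they are collected. The article lists no full set of baseline variables, so availability of items such as sex, angina class, prior MI or CTO complexity must be confirmed.
- **Role of baseline.** Because the groups are self-selected, report both the baseline-adjusted and the change-score version, and say beforehand which is primary.
- **MACE.** Use propensity weighting or a small covariate set suited to the number of events. No event count is given, so a long covariate list may not be supportable.
- **Unadjusted tests.** Keep them as descriptive.
- **Conclusions (section 10).** Claim an adjusted association, subject to unmeasured confounding, in place of the optimal modality.

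**Cost.** A little more analysis work, a possibly smaller or less precise estimate, and a more modest conclusion. No additional patients are needed. Adjustment will not remove confounding by factors that were not measured.
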